# Effect of ultrasound-guided injection of botulinum toxin type A into shoulder joint cavity on shoulder pain in poststroke patients: study protocol for a randomized controlled trial

**DOI:** 10.1186/s13063-024-08258-8

**Published:** 2024-06-27

**Keywords:** Stroke, Botulinum toxin type A, Hemiplegic shoulder pain, Randomized controlled trial, Protocol

## Abstract

**Background:**

Hemiplegic shoulder pain (HSP) is a common complication after stroke. It severely affects the recovery of upper limb motor function. Early shoulder pain in hemiplegic patients is mainly neuropathic caused by central nerve injury or neuroplasticity. Commonly used corticosteroid injections in the shoulder joint can reduce shoulder pain; however, the side effects also include soft tissue degeneration or increased tendon fragility, and the long-term effects remain controversial. Botulinum toxin injections are relatively new and are thought to block the transmission of pain receptors in the shoulder joint cavity and inhibit the production of neuropathogenic substances to reduce neurogenic inflammation. Some studies suggest that the shoulder pain of hemiplegia after stroke is caused by changes in the central system related to shoulder joint pain, and persistent pain may induce the reorganization of the cortical sensory center or motor center. However, there is no conclusive evidence as to whether or not the amelioration of pain by botulinum toxin affects brain function. In previous studies of botulinum toxin versus glucocorticoids (triamcinolone acetonide injection) in the treatment of shoulder pain, there is a lack of observation of differences in changes in brain function. As the content of previous assessments of pain improvement was predominantly subjective, objective quantitative assessment indicators were lacking. Functional near-infrared imaging (fNIRS) can remedy this problem.

**Methods:**

This study protocol is designed for a double-blind, randomized controlled clinical trial of patients with post-stroke HSP without biceps longus tenosynovitis or acromion bursitis. Seventy-eight patients will be randomly assigned to either the botulinum toxin type A or glucocorticoid group. At baseline, patients in each group will receive shoulder cavity injections of either botulinum toxin or glucocorticoids and will be followed for 1 and 4 weeks. The primary outcome is change in shoulder pain on the visual analog scale (VAS). The secondary outcome is the assessment of changes in oxyhemoglobin levels in the corresponding brain regions by fNIRS imaging, shoulder flexion, external rotation range of motion, upper extremity Fugl-Meyer, and modified Ashworth score.

**Discussion:**

Ultrasound-guided botulinum toxin type A shoulder joint cavity injections may provide evidence of pain improvement in patients with HSP. The results of this trial are also help to analyze the correlation between changes in shoulder pain and changes in cerebral hemodynamics and shoulder joint motor function.

**Trial registration:**

Chinese clinical Trial Registry, ChiCTR2300070132. Registered 03 April 2023, https://www.chictr.org.cn/showproj.html?proj=193722.

## Background and rationale {6a}

Hemiplegic shoulder pain (HSP) is a relatively common complication after stroke, with a prevalence of 16–84% [1]. HSP usually occurs within 12 weeks after stroke, which can seriously affect the recovery of upper limb motor function [2] and reduce the quality of life of patients [3]. Previous studies have shown that the pathogenesis of HSP is considered to be multi-factor, and paralysis is considered as the main cause of shoulder pain [4]. The current academic opinion suggests that HSP is more likely to be caused by neuropathic pain, which is caused by dysfunctional transmission and signal processing of the nervous system [5, 6].

At present, the treatment methods for HSP include local massage, physiotherapy, motor function training, and oral drugs [7, 8], among which local injection of glucocorticoids is considered a good way to reduce shoulder pain [9], and ultrasound-guided injection increases safety and efficacy [10]. However, the side effects of glucocorticoids injection also include soft tissue degeneration or increased tendon fragility [11]. Botulinum toxin local injection is a new way in HSP treatment [12]. Botulinum toxin acts directly on sensory neurons, which can modulate both muscle hyperactivity and pain caused by sensory impairment due to neurological damage. As a new treatment for pain, Botox does not cause side effects such as degeneration of the tendons and ligaments around the shoulder joint. Related studies have confirmed that injection of botulinum toxin into the muscles surrounding the shoulder joint (especially the subscapularis or pectoralis major) can reduce hemiplegic shoulder pain symptoms by decreasing muscle tone [13–15]. However, intramuscular injection of botulinum toxin has limitations such as exacerbating muscle atrophy [16], dose degradation [17], and unsuitable for patients with low muscle tension [18]. On the other hand, intra-articular drug injections have shown its simplicity, efficacy, safety, and ease of acceptance by patients [19, 20]. The mechanism of joint injection is mainly thought to block the conduction of pain receptors [21] in the shoulder joint cavity, reduce neurogenic inflammation by inhibiting neuropathic pain-inducing substances, and prevent peripheral and central sensitizing factors [22]. However, intra-articular botulinum toxin injections for HSP was rarely seen so far. In previous studies of botulinum toxin versus glucocorticoids in the treatment of shoulder pain, there is a lack of research on the mechanisms of the two drugs in improving pain and a lack of studies observing changes in brain function and the degree of muscle atrophy associated with treatment.

Visual analogue scale (VAS) is the main method used to evaluate pain. However, due to the lack of quantitative indicators as a basis for objective evaluation of HSP, some patients have poor cooperation with subjective evaluation. On the other hand, the existing assessment cannot analyze the mechanism of treatment. Therefore, we choose functional near-infrared imaging (fNIRS) as a secondary evaluation indicator. fNIRS is a technique for non-invasive measurement of cortical hemodynamics. fNIRS systems can monitor changes in local oxyhemoglobin concentration (HBO) caused by neurovascular coupling mechanisms [23]. To assist us in understanding how the brain works, we analyzed the areas of the brain that are activated during specific tasks. A correlation between cortical activation status and pain in patients with osteoarthritis of the knee has been found by fNIRS [24]. In another study of knee osteoarthritis using fNIRS, an increase in cortical blood flow activity was found to be elicited with increased knee pain [25]. Theoretical studies suggest that shoulder pain with stroke patients can be attributed to alterations in the central system associated with persistent pain in the shoulder joint and that persistent pain may induce reorganization of cortical sensory or motor centers [26]. The prefrontal cortex is thought to be the main brain region involved in pain modulation and pain activation [27, 28], receiving bottom-up pain input [29]. In Becerra et al., they used fNIRS to observe hemodynamic changes in bilateral prefrontal and sensory cortex during painful stimuli in healthy subjects [30]. Yucel et al. concluded that the increase in HbO in bilateral primary sensory area (S1) brain regions was only associated with injurious painful stimuli and not with non-injurious stimuli [31]. Related studies have confirmed that by fNIRS signal analysis, pain-related activation regions can be identified in the prefrontal cortex due to the fact that pain stimuli can induce an increase in both oxyhemoglobin and total hemoglobin content in the prefrontal cortex bilaterally [32]. The mechanism of improvement of hemiplegic shoulder pain by different drugs is not clear, and it has not been studied whether shoulder injection therapy affects the activity of different brain regions.

In our study, the aim is to investigate whether intra-articular injections of botulinum toxin into the shoulder cavity are more effective than glucocorticoids in improving pain. fNIRS assessment can increase our understanding of the mechanism of botulinum toxin treatment for HSP and can better provide an objective and reliable basis for clinical treatment.

### Objectives {7}

The primary aim is as follows: to investigate whether shoulder joint cavity injection of botulinum toxin compared with corticosteroids (tretinoin acetate) significantly improves shoulder pain in patients with HSP without biceps tendinitis or acromionic bursitis.

The secondary aims are as follows: in patients with HSP without tendon synovitis or acromioclavicular bursitis, does shoulder joint cavity injection of botulinum toxin type A significantly affect cerebral hemodynamics, improve Fugl-Meyer upper limb motor function, improve passive shoulder motion, and improve Ashworth scale scores compared to glucocorticoids (tretinoin acetate)?

### Trial design {8}

We are planning to conduct a single-center, randomized, double-blind, active-controlled clinical trial. Eligible participants will be randomly allocated in a 1:1 ratio into either the experimental group or the control group. The experimental group will be injected with botulinum toxin in the shoulder joint cavity, and the control group will be injected with glucocorticoids. The trial protocol will follow the Standard Protocol Item: Recommendations for Interventional Trials (SPIRIT 2013) guidelines.

## Methods and analysis

### Study setting {9}

The study is a 4-week randomized, double-blind controlled trial (Fig. 1). The research center is the Zhujiang Hospital of Southern Medical University, which has received the ethics approval (reference number:2022-KY-269–03). All patients in this study will be required to provide informed consent prior to data collection. Trials will be reported in accordance with CONSORT guidelines.

**Fig. 1 Fig1:**
[figure not shown]
Flowchart of the trial

### Eligibility criteria {10}

Inclusion criteria:Conform to the diagnostic criteria of stroke in Diagnostic Essentials of Major Cerebrovascular Diseases in China 2019; the diagnosis was confirmed by craniocerebral CT or MRI examination.First onset of stroke, age 18–80 years old, duration ≤ 6 months.Visual analog scale (VAS) for pain during passive abduction or external rotation of shoulder joint ≥ 4 points.Shoulder joint drug injection was not performed in half a year.The modified Ashworth scale for external rotation or abduction of shoulder joint was rated between 0 and 1 + Ultrasound of shoulder joint: the patient showed no accompanying acromion-deltoid slide bursitis or biceps brachialis tendinitis.There are no other bone, joint, and muscle diseases or other neurological diseases that significantly affect motor function.No obvious communication and understanding obstacles, able to carry out normal communication and cooperate with the completion of the experiment.The vital signs are stable and can cooperate with the examination.

Exclusion criteria.llergy to botulinum toxin or glucocorticoid.Intra-articular glucocorticoid or botulinum toxin injection of shoulder in the last 6 months.Previous history of shoulder joint surgery, frozen shoulder, rotator cuff injury, and shoulder joint trauma.Have other diseases more painful than hemiplegia shoulder pain.Active malignant tumors.Coagulopathy, diabetes mellitus, gastric ulcer, infection (within the last 6 months).Currently taking oral glucocorticoids, non-steroidal anti-inflammatory drugs, or immunosuppressive drugs.Pregnant and lactating women.With severe cognitive impairment, Minimum Mental State Examination (MMSE) score less than 21.Those who have not signed the informed consent.

### Who will take informed consent? {26a}

Participants are briefed about the trial before the trial began, and if the patient consented, a written informed consent stating that the patient willing to participate will be obtained.

### Additional consent provisions for collection and use of participant data and biological specimens {26b}

Not applicable. The study used primarily subjective scales to assess efficacy, and the trial did not involve collection of biospecimens for storage.

## Intervention

### Explanation for the choice of comparators {6b}

Local injection of botulinum toxin is an effective method for the treatment of shoulder pain. In order to reduce the time and energy spent in the hospital, we selected a single injection of botulinum toxin to verify its value in the treatment of hemiplegic shoulder pain.

### Intervention description {11a}

Patients will be randomly assigned to experimental group (botulinum toxin) or a control group (triamcinolone acetate). Each group received an injection at baseline. The experimental group will be given the injection of botulinum toxin in the shoulder joint cavity, the injection dose is 100 IU, and 2 ml normal saline will be mixed in advance, that is, the total drug is 2 ml. The control group will receive injections of triamcinolone acetate into the shoulder joint cavity, and 2 ml of total drug will also be injected into the shoulder joint cavity of the control group, including 1 ml of triamcinolone acetate and 1 ml of normal saline.

Injections of botulinum toxin or triamcinolone acetate into the shoulder joint cavity will be operated under ultrasound guidance. The process is as follows: (1) patient in lateral position, the affected shoulder to the top, and the affected hand is placed on the healthy side of the chest; (2) the ultrasound probe is placed transversely under the scapular spine and swept anteriorly and posteriorly to reveal the infraspinatus muscle and the articular glenoid; (3) routinely disinfect the towel, hold the probe in one hand, hold the syringe in the other hand, use the lower part of the external scapular spine as the entry point (Fig. 2), and enter the needle inwards (Fig. 3); (4) place the needle in the shoulder joint cavity under ultrasound guidance and slowly push the drug.

**Fig. 2 Fig2:**
[figure not shown]
Position diagram of ultrasonic probe and needle

**Fig. 3 Fig3:**
[figure not shown]
Ultrasound-guided intra-articular injection of shoulder

### Criteria for discontinuing or modifying allocated interventions {11b}

There will be no special criteria for discontinuing or modifying allocated interventions.

## Strategies to improve adherence to interventions {11c}

In this study, all treatments will be performed by the investigators. All treatments will be recorded and reported in the adherence instructions.

### Relevant concomitant care permitted or prohibited during the trial {11d}

During the trial, injections of any analgesics or oral analgesics into the shoulder are not allowed.

### Provisions for post-trial care {30}

If participants are injured or suffer any discomfort as a result of this study, they are entitled to free treatment and/or compensation for injuries related to this clinical study in accordance with Chinese law.

### Outcomes {12}

All assessments (VAS, upper limb Fugl-Meyer scores, passive range of motion (ROM) improvement, spasticity (MAS) improvement) and information regarding painkiller use will be applied at the baseline and 1-week and 4-week follow-up visits. The VAS pain assessment is the level of pain experienced by the patient during the past week of passive shoulder motion. fNIRS assessments include dorsolateral prefrontal area (DLPFC), primary motor area (M1), primary sensory area (S1), and oxyhemoglobin versus total hemoglobin levels, which will be checked at baseline and 1-week and 4-week follow-up. Other measures including demographics, history taking, and ultrasound of the shoulder joint in the study will be recorded at screening only. Adverse events are documented as described in the results.

#### *VAS* score

Shoulder pain will be assessed using a 100-mm VAS (1 point per 1 mm). Shoulder pain will be measured under passive abduction and passive external rotation. The standard question used is “How would you rate the pain level in your shoulder joint during this movement?”.

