### Sample size {14}

This study is a randomized controlled trial with botulinum toxin injections in the experimental group and glucocorticoid (tretinoin acetate) injections in the control group. The main regression indicator observed is the VAS pain score.

In this study, the sample size will be calculated with reference to similar relevant literature and pre-experimental results. The sample size will be calculated using two independent sample mean validity tests using the G-Power version 3.1.2 software. It is assumed that the means of the two groups are equal at baseline, that there is a 1-point difference in VAS pain score between the two groups at the first post-treatment assessment, and that the standard deviation of the two groups was 1.4, which should be consistent at each subsequent assessment, measured as an effect size (i.e., Cohen *d*, 0.71). Based on these magnitudes, alpha = 0.05 two-tailed is set. To achieve 80% efficacy, 32 patients per group will be counted as study subjects. To compensate for potential loss to follow-up, approximately 20% of patients will be added, with a final inclusion target of 78 patients (39 in each group).

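### The VAS is scored 0–100, but the entry criterion and planning values fit together only if a point is a tenth of the line; the three sections need one unit

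*Protocol article*

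**What the plan says.** The abstract names the primary outcome: "The primary outcome is change in shoulder pain on the visual analog scale (VAS"). The scale is defined in one place only, the VAS score section under Outcomes {12}: "Shoulder pain will be assessed using a 100-mm VAS". The parenthesis that follows sets the unit: "Shoulder pain will be assessed using a 100-mm VAS (1 point per 1 mm"). A point is therefore one millimetre, and the range is 0 to 100.

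Two other sections give VAS figures in points:

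- Eligibility criteria {10}: "Visual analog scale (VAS) for pain during passive abduction or external rotation of shoulder joint ≥ 4 points".
- Sample size {14}: "there is a 1-point difference in VAS pain score between the two groups at the first post-treatment assessment", and "the standard deviation of the two groups was 1.4", which the section turns into a Cohen d of 0.71, 32 patients per group and 78 in total.

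No section mentions a 0–10 scale, scoring in centimetres, or a conversion between the two.

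**The concern.** The same word, point, is used in all three sections, but the figures do not fit the definition given for it. A threshold of 4, a difference of 1 and an SD of 1.4 are ordinary values on a 0–10 pain scale and very small ones on 0–100.

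Two things depend on the unit:

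- **Who qualifies.** Someone who applies the eligibility and scoring sections as written would admit a patient scoring 4 of 100, who can improve by at most 4 points. Someone who takes a point as a tenth of the line would require ten times that mark. The two would enrol different populations.
- **What the target difference means.** As written, the difference on which the trial is planned is 1 mm on a 100-mm line. A reader of the final report needs to know whether the planned effect was 1 mm or 10 mm.

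There is also a recording risk. Data management {19} has two testers assess each subject, and an unsettled unit leaves room for ten-fold discrepancies in the primary outcome.

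**Working it through.** **Inputs.** Scale: 100 mm, one point per mm (VAS score section). Entry: at least 4 points (Eligibility criteria {10}). Difference 1 point, SD 1.4, two-sided alpha 0.05, power 80%, 32 per group, about 20% added, 78 in total (Sample size {14}). Allocation 1:1 (Trial design {8}).

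**Step 1: reproduce the plan's sample size.**

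- d = difference / SD = 1 / 1.4 = 0.714, stated as 0.71.
- Two-sample t test with d = 1/1.4: n = 31.76 per group, rounded up to 32.
- Power at 32 per group: noncentrality = d × √(n/2) = 0.714 × √16 = 2.857 on 62 degrees of freedom, giving 80.3%. With d rounded to 0.71 the results are n = 32.1 and 79.8%, an immaterial difference.
- Adding 20%: 32 × 1.2 = 38.4, rounded up to 39; 2 × 39 = 78.

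The stated figures reproduce.

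**Step 2: read each figure under both units.**

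| Figure | Point = 1 mm (as defined) | Point = one tenth of the line (inferred) |
|---|---|---|
| Entry, 4 points | 4 mm, 4/100 = 4% of the line | 40 mm, 4/10 = 40% |
| Difference, 1 point | 1 mm, 1% | 10 mm, 10% |
| SD, 1.4 points | 1.4 mm, 1.4% | 14 mm, 14% |

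Every row differs by a factor of ten.

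**Step 3: are the literal figures plausible together?** If scores are roughly normal, about 95% lie within 2 SD of the mean, a span of 4 × 1.4 = 5.6 points. Under the stated definition that is 5.6 mm of a 100-mm line, although the entry criterion has no upper limit and so admits anything from 4 to 100. With a point worth a tenth of the line, the span is 5.6 of 10 with entry from 4 to 10. The second set of figures hangs together; the first does not.

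**Step 4: does the unit change the sample size?** Re-expressed on 0–100, d = 10 / 14 = 0.714. This again gives 32 per group and 80.3% power. Multiplying every score by ten also leaves the t tests and the repeated measures ANOVA in Statistical methods {20a} unchanged, because effect and error scale together.

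**The case against.** The strongest reply is that this is a one-word slip with no statistical consequence. The eligibility and sample size figures agree with each other and the scoring definition is the odd one out, so the parenthesis may simply say millimetre where centimetre was meant. On that reading the entry threshold stands as written. The sample size, power and planned tests do not depend on the unit. The screening form and case report form are not shown and may already fix it.

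Much of this stands, and it rules out three stronger readings that a reader might infer:

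- **That the entry threshold is ten times too low.** This holds only if the 0–100 definition is what the sponsor means and the threshold was written for another scale. The 0–10 scale is inferred from the size of the numbers and is stated nowhere, so the documents do not show which section is wrong.
- **That the trial is badly underpowered.** That would require pairing a 1-mm difference with an SD taken from a 0–100 scale. Sample size {14} does not do this: it gives difference and SD together, with their ratio, in one unit.
- **That the arithmetic is wrong.** It is not; the calculation reproduces.

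The reply does not remove the contradiction. The article states the unit explicitly, and in a way that excludes reading a point as a centimetre, then uses figures that do not fit it. This is not detail left to a fuller document; it is a conflict within the text. A form that happens to carry the right unit would limit the harm but would not make the protocol consistent.

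**Conclusion.** The point holds as an internal inconsistency in the unit of the primary outcome. The scoring definition is incompatible with the entry criterion and the planning values by a factor of ten: 4% against 40% of the line for entry, 1 mm against 10 mm for the planned difference, and 1.4 mm against 14 mm for the SD.

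The conflict with the stated definition is on the face of the text. That a point was meant to be a tenth of the line is an inference from the plausibility of the three figures, and where the slip lies remains open. The effect is on who qualifies and on how the target difference is read. There is none on the sample size (32 per group before the allowance for loss, 78 in total), on power (80.3%) or on the planned tests.

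**What to change.** The sponsor should state which unit is meant and reconcile the three sections to it, by one of two routes:

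- change the scoring unit in the VAS score section; or
- keep the 0–100 scoring and re-express the figures in Eligibility criteria {10} and Sample size {14} on that scale.

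Which route is right is for the sponsor to say, and no entry threshold is proposed here. The chosen unit should also be the one used at screening and in data recording. Because the planned recruitment start was 1 March 2024, the sponsor should confirm which unit was applied to any patient already screened.

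The cost is a wording amendment, submitted to the ethics committee as the article's section on protocol amendments {25} requires, and a check of the forms. The design, N and analysis do not change.
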